## Abstract

**Background:**

All current approved antipsychotic drugs against schizophrenia spectrum disorders share affinity for the dopamine receptor (D2R). However, up to one-third of these patients respond insufficiently, and in some cases, side-effects outweigh symptom reduction. Previous data have suggested that a subgroup of antipsychotic-naïve patients will respond to serotonin 2A receptor (2AR) blockade.

**Aims:**

This investigator-initiated, translational, proof-of-concept study has overall two aims; 1) To test the clinical effectiveness of monotherapy with the newly approved drug against Parkinson's disease psychosis, pimavanserin, in antipsychotic-free patients with first-episode schizophrenia spectrum disorders; 2) To characterize the neurobiological profile of responders to pimavaserin.

**Materials and Equipment:**

Forty patients will be enrolled in this 6-week open label, one-armed trial with the selective serotonin 2AR antagonist (pimavanserin 34 mg/day). At baseline, patients will undergo: positron emission tomography (PET) imaging of the serotonin 2AR using the radioligand [¹¹C]Cimbi-36; structural magnetic resonance imaging (MRI); MR spectroscopy of cerebral glutamate levels and diffusion tensor imaging; cognitive and psychopathological examinations; electrocardiogram, and blood sampling for genetic- and metabolic analyses.

**Outcome Measures:**

The primary clinical endpoint will be reduction in the Positive and Negative Syndrome Scale (PANSS) positive score. Secondary clinical endpoints comprise multiple clinical ratings (positive and negative symptoms, depressive-, obsessive-compulsive symptoms, quality of life, social functioning, sexual functioning, and side-effects). PET, MRI, and cognitive parameters will be used for in-depth neuropsychiatric characterization of pimavanserin response.

**Anticipated Results:**

Clinically, we expect pimavanserin to reduce psychotic symptoms with similar effect as observed with conventional antipsychotics, for which we have comparable historical data. We expect pimavanserin to induce minimal side-effects. Neurobiologically, we expect psychotic symptom reduction to be most prominent in patients with low frontal serotonin 2AR binding potential at baseline. Potential pro-cognitive and brain structural effects of pimavanserin will be explored.

**Perspectives:**

Sub-Sero will provide unique information about the role serotonin 2AR in antipsychotic-free, first-episode psychosis. If successful, Sub-Sero will aid identification of a “serotonergic subtype” of schizophrenia spectrum patients, thereby promoting development of precision medicine in clinical psychiatry.

**Clinical Trial Registration:**

ClinicalTrials, identifier NCT03994965.

## Introduction

While the pathophysiology of schizophrenia is complex, all currently marketed pharmacological treatment options share dopamine D2 receptor (D2R) affinity. The neurobiological complexity of psychosis is indirectly reflected in the fact that up to one third of the patients with schizophrenia spectrum disorders do not respond sufficiently to dopaminergic drugs. Furthermore, in some patients the side-effects related to D2R antagonism outweigh the symptom reduction.

Clinically, schizophrenia spectrum disorders, such as schizophrenia, schizoaffective disorder, and schizotypy are often associated with life-long symptoms. The clinical features comprise positive psychotic symptoms (e.g. hallucinations and delusions), negative symptoms (e.g. anhedonia and social withdrawal), and marked cognitive deficits. Although current antipsychotics can reduce positive symptoms, the negative symptoms and cognitive deficits are relatively unaffected or may even worsen during treatment (Nørbak-Emig et al., 2016).

D2R antagonism is associated with extrapyramidal side-effects, hyperprolactinemia (Coello et al., 2015), dyslipidemia (Ebdrup et al., 2014), weight gain (Nielsen et al., 2016), as well as subcortical structural brain changes (Ebdrup et al., 2013). Moreover, D2R antagonism may induce tardive dyskinesia and secondary cognitive impairments, and the extrapyramidal side-effects reduce compliance all of which increase the risk of relapse (Meltzer, 2013). Finally, the metabolic side-effect may contribute to the reduced life expectancy of 15–20 years for patients with severe mental disorders (Nordentoft et al., 2013). Considering the severity of these side-effects, ideally, D2R antagonists should only be prescribed to patients, who respond to these drugs. Unfortunately, at present alternative drug treatment strategies are not available. Beyond the shared feature of D2R affinity, most marketed antipsychotics have a more expansive neuro-receptor profile. More specifically, several of the so-called second-generation antipsychotics, e.g. quetiapine, olanzapine, lurasidone, and clozapine are characterized by a relatively low D2R affinity combined with a relatively high serotonin 2AR affinity (Meltzer and Massey, 2011).

In 1957, Carlsson presented evidence that dopamine is a neurotransmitter, and in 1977, he further hypothesized that dopamine hyperfunction may underlie psychotic symptoms in schizophrenia (Carlsson, 1977). The dopamine hypothesis of schizophrenia has been modified over time and the more recent version suggests that schizophrenia patients, who respond to conventional dopamine D2R antagonists, may have an increased dopamine synthesis- and release capacity in the basal ganglia (Howes and Kapur, 2009). Conversely, non-responders to dopamine antagonists may constitute a neurobiologically different subtype.

The involvement of the 5-hydroxytryptamine 2A receptor (serotonin 2AR) system in schizophrenia was proposed in 1954. The hypothesis was based on the observations that lysergic acid diethylamide (LSD) can induce hallucinations and emotional disturbances, which are common clinical features of schizophrenia, and it was discovered that LSD was a potent serotonin 2AR agonist (Woolley and Shaw, 1954).

In 2010, we published the hitherto largest *in vivo* positron emission tomography (PET) study of initially antipsychotic-naïve, first-episode schizophrenia patients, and our findings confirmed the presence of a reduced serotonin 2AR availability in the frontal cortex (Rasmussen et al., 2010). Moreover, before treatment, the cerebral serotonin 2AR availability was inversely associated with the severity of psychotic symptoms (Rasmussen et al., 2010). After treatment with the antipsychotic compound, quetiapine, we found that the reduction in psychotic symptoms was related to the cerebral serotonin 2AR occupancy (Rasmussen et al., 2011). Overall, data from this cohort study supported that a proportion of schizophrenia patients may be responsive to selective serotonin 2AR blockade (Meltzer et al., 2004; Geyer and Vollenweider, 2008). An independent twin study further confirmed that low frontal serotonin 2AR availability may be a state feature of schizophrenia (Rasmussen et al., 2016). Indirect clinical support for a serotonergic target at the earliest disease stage is, that psychosis induced by serotonin 2AR agonism resembles first-episode schizophrenia more than chronic schizophrenia (Geyer and Vollenweider, 2008). Moreover, clozapine, which is the most effective antipsychotic drug, has pronounced antagonism at the serotonin 2AR, and this feature has been suggested to contribute to its superiority (Steward et al., 2004). Finally, genetic studies of serotonin 2A single-nucleotide polymorphism in schizophrenia support the role of the serotonin 2A receptor gene in schizophrenia and the response to antipsychotic drugs (Serretti et al., 2007; Kaur et al., 2017).

In an independent cohort of antipsychotic-naïve patients, we recently provided proof-of-concept to support the notion of subtyping schizophrenia. By means of advanced multimodal and multivariate algorithms on electrophysiological and cognitive data, we identified two distinct subtypes of patients. Before treatment the two subtypes were clinically inseparable, yet their response to selective dopaminergic blockade was predicted with significant accuracy (Bak et al., 2017).

Based on the above, we hypothesize that the clinical effect with monotherapy with a selective 2AR antagonist will be similar to the effect seen with treatment with a D2R antagonist, for which we have comparable, comprehensive historical data. Specifically, we expect psychotic symptom reduction to be most prominent in the patients with the lowest frontal serotonin 2AR binding potential at baseline. With Sub-Sero, we aim to identify a subtype of patient with schizophrenia spectrum disorders, which, if successful, will guide a personalized medicine approach to treating schizophrenia spectrum patients at the earliest stage of the disorder.

## Materials and Equipment

### Study Medication

Pimavansin (Nuplazid™) is a selective serotonin 2AR antagonist with the recent indication of treatment of hallucinations and delusions associated with Parkinson's disease psychosis (FDA approval, April 2016).

Pimavanserin acts as an inverse agonist and antagonist at serotonin 2A receptors with high binding affinity (Ki value 0.087 nM) and at serotonin 2C receptors with lower binding affinity (Ki value 0.44 nM). Pimavanserin has low affinity for sigma 1 receptors (Ki value 120 nM) and has no appreciable affinity (Ki value >300 nM) to dopaminergic (including D2), serotonin 2B, muscarinic, histaminergic, or adrenergic receptors, or to calcium channels. The mean plasma half-lives for pimavanserin and the active metabolite (N-desmethylated metabolite) are approximately 57 and 200 h, respectively. This results in stable plasma concentrations with only one tablet a day. The median time to maximum concentration (T_max_) of pimavanserin is 6 h and independent of dose. Absorption is independent of meal ingestion. In human plasma, the distribution pimavanserin is predominantly protein bound (~95%) (Vanover et al., 2007).

### Side-Effects

Side-effects in placebo-controlled studies of 6-week treatment (N=202) comprise nausea 7%, constipation 4%, peripheral oedema 7%, gait disturbance 2%, hallucination 5%, and confusion 6% (Vanover et al., 2007). After approval of pimavanserin, somnolence, rash, urticaria, and reactions consistent with angioedema (e.g., tongue swelling, circumoral oedema, throat tightness, and dyspnoea) have only been sporadically reported (Fda, 2017).

Pimavanserin prolongs the QT interval, and although no other ECG abnormalities have been linked to pimavanserin, treatment should be avoided in patients with known QT prolongation or in combination with other drugs known to prolong QT interval (Ballard et al., 2018).

### Clinical Data on Pimavanserin

We conducted a literature search on [pimavanserin AND schizophrenia] in the databases PubMed and ClinicalTrials for the results of studies on pimavanserin and the effect on schizophrenia spectrum patients (search date: July 16^th^, 2019). The PubMed search resulted in 26 hits: 6 reviews on possible use in schizophrenia; 8 hits related to Parkinson's Disease; one commentary article, and the 2 original papers, which are summarized below.

The ClinicalTrials search resulted in 14 hits. Besides the current study protocol and the study by Meltzer et al. mentioned below, three studies are currently investigating the effect of pimavanserin as add on therapy for schizophrenia patients (NCT03121586; NCT02970292; NCT02970305). All are initiated by the manufacturer ACADIA Pharmaceuticals. The ten remaining studies were in patients with Parkinson's and Alzheimer's diseases. The current Sub-Sero trial (NCT03994965) will be the first study to use pimavanserin as monotherapy in schizophrenia spectrum patients.

In 2012, Meltzer et al. published a randomized double blinded trial that examined the potential efficacy of pimavanserin as an add-on treatment to risperidone and haloperidol, respectively, compared with risperidone as monotherapy (Meltzer et al., 2012). The study was conducted on 423 patients with chronic schizophrenia and a recent exacerbation of psychotic symptoms. Patients were randomized in four groups and treated for 6 weeks of risperidone 2 mg + placebo, risperidone 2 mg + pimavanserin 20 mg, risperidone 6 mg + placebo, haloperidol 2 mg + placebo, or haloperidol 2 mg + pimavanserin 20 mg. The reduction in Positive and Negative Syndrome Scale (PANSS) total score with risperidone 2 mg + pimavanserin by end of study was significantly greater than risperidone 2 mg + placebo: −23.0 vs. −16.3 (p=0.007), and there was no significant difference from the risperidone 6 mg + placebo group. Weight gain and hyperprolactinemia were greater in the risperidone 6 mg + placebo group than the risperidone 2 mg + pimavanserin group, but there was no difference in extrapyramidal side-effects. Overall, the study supported preclinical data (Gardell et al., 2007) indicating that serotonin 2A antagonism has potential as add-on treatment, which may enable dose reduction of conventional antipsychotics.

In 2019, Nasrallah et al. published an open label case series of 10 patients with refractory psychosis successfully treated with add-on pimavanserin to their usual treatment (Nasrallah et al., 2019). Six of the patients had previously tried, but not responded to clozapine. All patients showed marked response to augmentation with pimavanserin 34 mg/day within 4–8 weeks. Improvements of negative symptoms and social functioning were also reported. None of the patients discontinued pimavanserin due to side-effects. Despite the open label, non-controlled design, these cases provide encouraging perspectives for usage of pimavanserin in schizophrenia patients and importantly pimavanserin appeared well-tolerated with a favorable side-effect profile.

## Methods

### Study Design

One-armed, open label, investigator-initiated, proof-of-concept trial.

### Study Population

#### Patients

We will include antipsychotic-free [no prior use of antipsychotics longer than two weeks in the previous year or 6 weeks lifetime, or antipsychotic treatment within 30 days prior to inclusion, same criteria as the OPTiMiSE cohort (Kahn et al., 2018)], first-episode schizophrenia spectrum patients. ICD-10 diagnoses are shown in **Table 1**. Patients will be recruited from psychiatric hospitals and outpatient psychiatric centers in the capital region (Copenhagen area). Before inclusion, diagnoses will be verified by schedules for clinical assessment in neuropsychiatry (SCAN) (Wing et al., 1990). In- and exclusion criteria are shown in **Table 1**.

**Table 1 T1:** In- and Exclusion Criteria in Sub-Sero.

Inclusion criteria
Antipsychotic-free^1^
Fulfilling diagnostic criteria of schizophrenia, persistent delusional disorder, acute and transient psychotic disorders, schizoaffective disorder, other non-organic psychotic disorders and unspecified non-organic disorders (ICD-10: F20.x; F22.x; F23.x; F24.x; F25.x; F28; F29)
Age: 18-45 years
Legally competent

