**Exclusion criteria**
Current substance dependence ICD-10 (F1x.2) or substance abuse in any period up to 3 months prior to referral (exception: tobacco/nicotine, F17.2)
Head injury with more than 5 minutes of unconsciousness
Any coercive measure
Metal implanted by operation
Pacemaker
Pregnancy (assessed by urine HCG)
Female patients: Unwillingness to use safe contraception (Intra Uterine Device/System or hormonal contraceptives) during the study period including the wash out period.
Severe physical illness
Known QT prolongation or congenital prolongation of the QT interval
Medical history of cardiac arrhythmias, as well as other circumstances that may increase the risk of torsade de pointes and/or sudden death, including symptomatic bradycardia, hypopotassemia or hypomagnesemia
Current treatment with drugs known to prolong QT interval^2^
Allergies to any of the inactive ingredients and film coat components^3^

^1^No prior use of antipsychotic medication longer than an episode of two weeks in the previous year and/or 6 weeks lifetime, and/or antipsychotic treatment within 30 days prior to inclusion (Kahn et al., 2018).

^2^Class 1A antiarrhythmics (e.g., quinidine, procainamide); Class 3 antiarrhythmics (e.g., amiodarone, sotalol); certain antibiotics (e.g., gatifloxacin, moxifloxacin).

^3^Pregelatinized starch, magnesium stearate, microcrystalline cellulose, hypromellose, talc, titanium dioxide, polyethylene glycol, and saccharin sodium.

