### Neuroimaging

#### Positron Emission Tomography (PET)

PET-scans using the radioligand tracer [¹¹C]Cimbi-36 will be conducted at Neurobiology Research Unit at Rigshospitalet in order to estimate the cerebral serotonin 2A receptor binding potential. The serotonin 2AR agonist PET radioligand [¹¹C]Cimbi-36 will be produced for human administration, as previously described (Ettrup et al., 2014). All participants will be scanned at baseline in a high-resolution research tomography (HRRT) PET scanner (CTI/Siemens, Knoxville, TN).

PET will not be repeated after 6 weeks. Instead, the relation between plasma pimavanserin and cerebral serotonin 2AR occupancy will be based on data obtained in 5 healthy volunteers: [¹¹C]Cimbi-36 PET will be performed before intake of a single dose of pimavanserin 34 mg. PET will be repeated twice within the next two days to determine the relation between cerebral serotonin 2AR occupancy and plasma-pimavanserin. By measuring patients' plasma- pimavanserin levels after 6 weeks, when in steady-state, we will use this plasma-pimavanserin/2AR occupancy ratio derived from the healthy controls to index patients' serotonin 2AR occupancy.

In order to compare baseline serotonin 2AR binding potential, patients will be compared with a group of comparable healthy historical controls balanced on age and gender from the CIMBI data-base (Knudsen et al., 2016).

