## Anticipated Results

### Sample Size Calculation

In Sub-Sero, we hypothesize that treatment with pimavanserin will have a similar clinical effect as was observed in a previous, comparable cohort in which patients underwent 6 weeks of treatment with amisulpride. Neurobiologically, we expect psychotic symptom reduction after pimavanserin treatment to be most prominent in patients with low frontal serotonin 2AR binding potential at baseline.

Our previous amisulpride cohort comprised 46 initially antipsychotic-naïve, first-episode schizophrenia patients. Details on the cohort are provided in, e.g. (Nielsen et al., 2012a; Nielsen et al., 2012b; Nielsen et al., 2016; Wulff et al., 2019). The 6 weeks of treatment with amisulpride, a dopamine D2R/D3R antagonist [with serotonin 7, but not serotonin 2A affinity (Abbas et al., 2009)], produced a mean reduction in PANSS positive score of 5.98 with a standard deviation of 4.68 (**Figure 1**). We have estimated a “trial effect” (or natural variation) to a reduction in PANSS positive to 2.5. With 46 patients treated with amisulpride for 6 weeks, the observed power was 95%.

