### Hypotheses

Patients treated with pimavanserin in monotherapy will display a comparable response as patients treated with a conventional dopamine D2 antagonist (amisulpride). Observed response to 6 weeks of amisulpride treatment is shown in **Figure 1** and is based on comprehensive historical data from our group (**Figure 1**).Pimavanserin will be well-tolerated and induce fewer side-effects (e.g. fewer EPS, minimal weight gain and minimal hyperprolactinemia) than amisulpride (compared with historical data).Neurobiologically, we expect psychotic symptom reduction to be most prominent in the patients with the lowest frontal serotonin 2AR binding potential at baseline.Pimavanserin will produce improvements in measures of attention, verbal fluency, executive function, and working memory.Pimavanserin will exert non-detrimental effects on brain structure.

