## Discussion

We anticipate that the Sub-Sero trial will contribute novel clinical and neuropsychiatric data from a cohort of antipsychotic-free, first-episode schizophrenia spectrum patients exposed to monotherapy with a selective 2AR antagonist.

The open-label study design of Sub-Sero is motivated by the fact that pimavanserin will be used off-label for a vulnerable group of antipsychotic-free, first-episode patients with schizophrenia spectrum disorder, who are challenging to recruit. Moreover, the current sparse level of evidence for efficacy of pimavanserin in this patient group remains to be demonstrated before embarking on a randomized controlled trial (RCT) design. Since clinical relevance is the highest priority in Sub-Sero, we chose psychotic symptom reduction as our primary outcome. We have no active control group, but the open label design permits us to compare treatment response with our previous cohorts, on which we have comparable and comprehensive data, e.g. see **Figure 1**.

Inherently, Sub-Sero should not be regarded a pivotal clinical trial. To truly estimate treatment effect of pimavanserin a double-blinded RCT is necessary. We argue that the burden of the disease in these vulnerable patients, along with the current insufficient treatment options justify this proof-of-concept trial with pimavanserin monotherapy.

We expect that Sub-Sero will provide unique information of the role serotonin 2AR in antipsychotic-free, first-episode psychosis, which may inform the design of future randomized clinical trials testing effectiveness of pimavanserin as monotherapy. If successful, Sub-Sero will aid identification of a “serotonergic subtype” of schizophrenia spectrum patients, thereby promoting the development of precision medicine for use in clinical psychiatric practice.

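### The amisulpride cohort is called comparable but differs from Sub-Sero on diagnosis and prior antipsychotic exposure, so the historical comparison can be confounded by case mix

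*Protocol article*

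**What the plan says.** **Sub-Sero population.** Table 1 of the protocol article (Study Population, Patients) admits ICD-10 F20, F22, F23, F24, F25, F28 and F29, worded as "Fulfilling diagnostic criteria of schizophrenia, persistent delusional disorder, acute and transient psychotic disorders, schizoaffective disorder, other non-organic psychotic disorders and unspecified non-organic disorders". Patients must be antipsychotic-free, which is not the same as naive. Footnote 1 sets the limit as "No prior use of antipsychotic medication longer than an episode of two weeks in the previous year and/or 6 weeks lifetime", with no antipsychotic treatment in the 30 days before inclusion. The text says these limits come from another cited cohort, not from the amisulpride cohort.

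**Historical cohort.** Sample Size Calculation states: "Our previous amisulpride cohort comprised 46 initially antipsychotic-naïve, first-episode schizophrenia patients". The legend of Figure 1 describes the cohort in the same way.

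**How the two are linked.** Sample Size Calculation expects a "similar clinical effect as was observed in a previous, comparable cohort". The Discussion accepts that there is no active control group and says that "the open label design permits us to compare treatment response with our previous cohorts, on which we have comparable and comprehensive data". Under Hypotheses, the first expects a response on a par with amisulpride, and the second expects fewer side-effects than with amisulpride, citing historical data.

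**Balancing.** The article mentions it once for a historical group, in the PET section, where patients are set against "healthy historical controls balanced on age and gender from the CIMBI data-base". Nothing equivalent is stated for the amisulpride comparison.

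**The concern.** The article makes a positive claim of comparability that its own eligibility criteria contradict on two counts: diagnosis (schizophrenia only against seven diagnostic groups) and treatment history (naive against limited prior exposure allowed).

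This matters because the trial has one arm. The amisulpride cohort is the only efficacy comparator for the hypothesis of similar response, and the comparator for the side-effect differences in the second hypothesis. If the additional diagnoses or the previously exposed patients have a different six-week course for reasons unrelated to the drug, the observed difference mixes case mix with drug. A shift in favour of Sub-Sero could make a weaker drug look equal to amisulpride. A shift the other way could make an equal drug look worse.

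**Working it through.** **1. The plan's own figure.** Inputs from Sample Size Calculation: mean reduction 5.98, SD 4.68, trial effect 2.5, alpha 0.05 (taken as two-sided), power 80%.

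- Planning difference: 5.98 − 2.5 = 3.48.
- Two-group normal formula, per group: n = 2 × (1.960 + 0.842)² × (4.68/3.48)² = 2 × 7.849 × 1.809 = 28.4, so 29. The article states 29.
- The same formula with 46 per group gives 94.6% power. The article states 95%.

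The arithmetic reproduces. The question is whether figures from a narrower population can serve as the benchmark.

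**2. The populations side by side.**

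| | Amisulpride cohort | Sub-Sero |
|---|---|---|
| Diagnosis | First-episode schizophrenia | F20, F22, F23, F24, F25, F28, F29 |
| Prior antipsychotics | None | Limited earlier exposure allowed, none within 30 days |
| Patients | 46 | 30 completers planned, 40 enrolled |

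**3. Precision of the comparison.** Assume SD 4.68 in both groups, with 30 completers against 46.

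- SE = 4.68 × √(1/30 + 1/46) = 4.68 × 0.2347 = 1.10.
- 95% half-width = 1.96 × 1.098 = 2.15 points.

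**4. Size of a case-mix shift (assumed; the documents give no figure).** If a share f of Sub-Sero patients changes by e points more or less for reasons unrelated to the drug, the mean shifts by f × e. With f = 20% and e = 5 the shift is 1.0 point. Over f = 10% to 30% and e = 2 to 6 it runs from 0.2 to 1.8 points. The sign can be positive or negative.

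**5. Effect on the comparison.** With no true drug difference and a shift b, the two-sided false-difference rate is Φ(b/SE − 1.96) + Φ(−b/SE − 1.96). It is the same for either sign of b.

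| Shift b (points) | 0 | 0.5 | 1 | 1.5 | 2 |
|---|---|---|---|---|---|
| False-difference rate | 5% | 7.4% | 14.9% | 27.7% | 44.5% |

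If the shift favours Sub-Sero, the chance of detecting a true 3-point deficit against amisulpride is Φ((3 − b)/SE − 1.96): 78% with no shift, 44.5% with a 1-point shift and 14.7% with a 2-point shift.

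**6. What adjustment can and cannot do.** A model with baseline PANSS positive, age and sex removes differences in those covariates. It cannot separate diagnosis or prior exposure from drug for the added patients, because the cohort as described contains no one with the other diagnoses and no one previously exposed. Only restriction addresses that. If half of 30 completers were F20 and naive (assumed), 15 against 46 gives SE = 4.68 × √(1/15 + 1/46) = 1.39 and a half-width of 1.96 × 1.39 = 2.73 points.

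**The case against.** The strongest reply has four parts.

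- *The analysis is not stated.* A reader might infer that the plan commits to an unadjusted comparison. It does not: the article names no estimator, covariates or restriction, and a fuller protocol or analysis plan may do so. This stands, so silence on adjustment is not the finding. What remains is the claim of comparability set against the stated criteria.
- *The primary endpoint is within-patient change.* A reader might infer that case mix undermines the primary result or a test against the trial effect of 2.5. The Primary Endpoint section defines only baseline minus week 6. The 2.5 appears only in the sample-size reasoning, its source population is not given, and no test against it is stated. This stands.
- *The direction is unknown.* It is tempting to argue that transient psychoses remit on their own and must raise the Sub-Sero mean. The documents give no course or recovery rate for any diagnosis, and they also admit persistent delusional disorder, schizoaffective disorder and previously exposed patients, who might shift the mean either way. This stands.
- *The limits are disclosed.* The Discussion says the trial is not pivotal and that a double-blind randomised trial is needed. That lowers the weight of the point. It does not answer it, because the same section does not mention the population difference and describes historical data "on which we have comparable and comprehensive data".

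Two smaller points also stand. The documents show no mechanism by which diagnosis or brief past exposure would change side-effect rates, so for hypothesis 2 confounding is a possibility only, and its statement that the drug will be well tolerated does not depend on the comparison. Nor is a loss of power shown if the SD is larger here: a one-sample test with 30 completers would keep about 80% power for 3.48 points up to an SD of roughly 6.6.

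**Conclusion.** The point holds for the historical comparison. The article calls the amisulpride data comparable, while its own criteria show a wider diagnostic range and a different treatment history. Hypothesis 1 and the comparative part of hypothesis 2 can therefore be confounded by case mix.

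The size rests on assumptions: SD 4.68 in both groups, 30 completers, and a shift the documents do not quantify. On those terms 1 point is about one standard error and takes the false-difference rate from 5% to about 15%. The mismatch does not affect the calculation of the primary endpoint, and neither a direction of bias nor a commitment to an unadjusted analysis can be read from the text. In a declared proof-of-concept trial this is a change that should be made, not one that invalidates the design.

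**What to change.** 1. In Sample Size Calculation and Discussion, replace the word comparable with a statement of the two differences: the cohort was schizophrenia only and antipsychotic-naive, whereas Sub-Sero admits further diagnoses and limited prior exposure.
2. Make the historical efficacy comparison on patient-level data, with week-6 PANSS positive as outcome, adjusted for baseline PANSS positive, age and sex. Keep the full enrolled cohort as the main comparison.
3. Prespecify a sensitivity comparison restricted to Sub-Sero patients with F20 and no prior antipsychotic exposure.
4. Report the mean PANSS positive reduction without F23 patients alongside the full-cohort mean.

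**Cost.** No new trial data are needed. Diagnoses are verified by SCAN before inclusion, PANSS is rated at baseline and week 6, and prior exposure must be established for eligibility. Patient-level access to the historical data is assumed, since the group describes the cohort as its own. The price is precision in the restricted comparison: about 2.7 points half-width against 2.15 if half of 30 completers qualify. It also covers only part of the enrolled population, which is why it should remain a sensitivity analysis.
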